### Primary outcome analysis

The target sample size is 120 randomized participants (60 per study arm). The sample size was based on our most recent IPS study at the Tuscaloosa VA Medical Center that evaluated IPS in the primary care setting as nearly half of the participants had a SUD diagnosis. We expect that more than 84% will complete the intervention as randomized and greater than 95% will provide analyzable employment data. The between-group effect size was 0.55 in favor of IPS in the prior study, for which our projected sample size (54 per group with > 2 months data) would provide > 81% power. Very conservatively assuming that only 90% provide analyzable data this yields approximately 54 participants per group. This provides 80% power to detect a difference in means between groups of 0.54 standard deviations for a continuous outcome. The primary employment outcome is the number of weeks with competitive employment over the 18-month follow-up period. A week scored as “worked” is one in which a competitive job was held for any number of hours or days during that week. A week scored as “not worked” is one in which there was no competitive job held, or there were no employment data (i.e., early exit or missing data). The analysis of the primary outcome will use longitudinal mixed-effects regression models considering the cumulative number of weeks worked at each assessment as the dependent variable and study arm (IPS vs. non-IPS-VR) as the main independent variable adjusted for gender. Study site will be treated as a random effect, as will participant to account for the nesting of participants within sites and the multiple observations per person. We will initially specify the covariance structure of the repeated outcomes as unstructured and will proceed respectively to autoregressive and exchangeable structures if convergence issues are encountered. Prior to final modeling we will examine longitudinal plots of the employment data by group to evaluate whether the most appropriate model and any possible interaction effect appears to be additive (linear regression) or multiplicative (suggesting negative binomial regression), whether time should be included as categorical or linear, and whether it appears that a group*time interaction term is required to faithfully model the data.

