### MOUD analyses

An additional aim is to compare IPS to non-IPS-VR in terms of adherence to MOUD and relapse into heavy opiate use. We expect that MOUD adherence can be treated as a continuous variable in regression models. However, prior to modeling we will examine its distribution, to determine if this is appropriate. Relapse will be treated in two ways, as a binary indicator if any relapse as determined by TAPS (defined as opioid misuse ≥ 4 times/mo.), and the total number of self-reported days of misuse. The first dichotomous outcome will require logistic regression. The second approach will depend on the observed distribution and may be treated as either negative binomial or continuous. We will also explore the differences between groups in rates of relapse. The exploratory analysis will construct longitudinal models similar to those in our first aim considering outcomes of weekly adherence and relapse with that week’s employment status as well as lagged employment status (e.g., employment in previous weeks) as covariates to more directly examine the possible role of employment outcomes in explaining adherence and/or relapse. Further analyses may also include psychosocial covariates.

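### The exploratory models linking employment to MOUD adherence and relapse do not separate within-person change in employment from stable differences between people who work more and people who work less

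*Protocol article*

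**What the plan says.** The last part of MOUD analyses in the protocol article sets out the model: "The exploratory analysis will construct longitudinal models similar to those in our first aim considering outcomes of weekly adherence and relapse". Employment enters "with that week’s employment status as well as lagged employment status (e.g., employment in previous weeks) as covariates", and the same sentence gives the purpose: the terms are used "as covariates to more directly examine the possible role of employment outcomes in explaining adherence and/or relapse".

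The first-aim model is described under Primary outcome analysis: "Study site will be treated as a random effect, as will participant to account for the nesting of participants within sites". The residual covariance starts as unstructured, and the analysts "will proceed respectively to autoregressive and exchangeable structures if convergence issues are encountered".

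No person-mean or centered employment term is named, and none is excluded. Psychosocial covariates are mentioned only as a possibility. The exploratory model has no stated alpha or decision rule; the 0.05 level in the article belongs to the primary hypothesis.

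**The concern.** A random-intercept model with a raw time-varying covariate assumes that the covariate is unrelated to each person's stable outcome level. Arm is randomized, but employment after randomization is not. Participants in more stable recovery may both work more and relapse less, whatever work itself does. The employment coefficient is then a weighted mix of a within-person contrast and a between-person contrast, and only the first bears on the stated purpose.

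What is at stake is interpretation. The Discussion presents the study as the first to look at vocational services, employment and MOUD adherence together. A significant employment coefficient would naturally be read as work supporting adherence or protecting against relapse, when stable differences between people could have produced part or all of it.

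**Working it through.** **The plan's own figure.** The article gives no error rate or power for this model. Its one calculation, for the primary outcome, reproduces. With 54 per group and d = 0.55, 0.55 × √(54/2) = 2.858; 2.858 − 1.960 = 0.898; Φ(0.898) = 0.815, against the stated figure of more than 81%. With d = 0.54 the result is 0.801, against 80%.

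**Inputs from the article**
- Sample: "The target sample size is 120 randomized participants (60 per study arm"), with about 54 per group analyzable, so 108.
- Weekly records: 18 months × 52/12 = 78.
- Visits: months 2 to 16 in steps of two, plus month 18, so 9 (Randomization and follow-up schedule).
- MOUD users: 16/41 = 39% at baseline so far (Table 3); 0.39 × 120 ≈ 47 if that share holds.
- Relapse: defined per month and measured with the TAPS-2 and pharmacy records (MOUD outcome assessment). The TAPS-2 is listed as a repeated measure, and visits are two-monthly. Relapse may therefore supply about 9 records per person, although the exploratory model speaks of weekly outcomes. Both cases are shown.

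**Assumed, because the article does not give them**
- Intraclass correlation (ICC) of 0.05 to 0.8.
- Correlation ρ between stable work propensity and stable outcome level of 0, 0.3 or 0.5.
- About 47% of weeks worked.
- Share s = 0.45 of employment variance lying between persons.
- Two-sided 5% tests.

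**Step 1: weight of the between-person contrast in the slope (linear random-intercept model).**
k = (1 − ICC)/(1 − ICC + T·ICC); weight = k·s/(k·s + 1 − s).

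Example with T = 9 and ICC = 0.2: k = 0.8/2.6 = 0.308; weight = 0.138/(0.138 + 0.55) = 20.1%.

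| ICC | 78 weekly records | 9 visits |
|---|---|---|
| 0.05 | 13.8% | 35.7% |
| 0.2 | 3.8% | 20.1% |
| 0.5 | 1.0% | 7.6% |
| 0.8 | 0.3% | 2.2% |

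**Step 2: rejection when employment has no effect.** Work and outcome were simulated to share only the stable trait. Models had arm, gender, time and a participant intercept; the site effect was omitted. Weekly fits used current and one-week-lagged status, shown as joint test / summed coefficient. Visit fits used current status only. There were 120 to 600 replicates per cell, so Monte Carlo error is about 1 to 3 points.

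| Design | ρ = 0.3 | ρ = 0.5 | ρ = 0.5 with person mean |
|---|---|---|---|
| Weekly, linear, N = 108, ICC 0.2–0.8 | 4.5–5.0% / 4.3–9.0% | 5.2–10.7% / 8.3–14.2% | 5.5% / 7.0% (ICC 0.2) |
| Weekly, linear, N = 108, AR(1) errors modeled, ICC 0.2–0.5 | 6.5–9.0% / 7.0–11.5% | 8.5–13.0% / 11.5–16.0% | 5.5–7.0% / 8.0–9.0% |
| Weekly, logistic, N = 108 | 5.8% / 10.0% | 10.8% / 13.3% | 3.3% / 5.0% |
| 9 visits, linear, N = 108 | 6.5–14.8% | 11–35% | 4.3% (ICC 0.2) |
| 9 visits, logistic, N = 108 | 12% | 31% | 5.0% |
| 9 visits, linear, N = 47, ICC 0.2–0.5 | 6–9% | 11–19% | not run |

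- Weekly records in 47 participants, both values of ρ, ICC 0.2–0.8: 3.5–5.0% / 3.7–6.5%.
- Weekly records, N = 108, at the very low ICC of 0.05: 10% / 15% (ρ = 0.3) and 22.5% / 28% (ρ = 0.5).
- ρ = 0: about 4–7% throughout, provided serial correlation is modeled.

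**Step 3: what the person mean does not repair.** With weekly residual autocorrelation of 0.5 or 0.8 left unmodeled, the joint test rejects in 21% or 39% even at ρ = 0. With the person mean added (run at ρ = 0.3) it still rejects in 20% or 39%.

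**The case against.** The strongest reply is that the article describes weekly outcomes. With 78 records per person the slope is 86% to more than 99% within-person at the ICCs tried, and for adherence in about 47 MOUD users the test is close to nominal. This stands. A reader might infer that the model simply compares workers with non-workers, or that it generally rejects far above 5%. The weekly design supports neither reading. Much higher rates can be produced, up to about 90% in visit-level simulations, but they need few records per person and a strong assumed correlation, and the article gives no figure for that correlation.

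The reply is weaker for relapse, where the per-month definition and two-monthly TAPS-2 leave about nine records as a plausible data structure.

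A second reply is that the analysis is labeled exploratory, carries no stated test, and could be refined in a fuller analysis plan. This also stands and lowers the severity. It does not remove the point, because the article does state which employment terms enter and what they are meant to show.

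A third reply is that the remedy is partial. A mean over all follow-up includes employment after the outcome. If relapse leads to job loss, the within-person term is biased too, and these simulations contained no such feedback. That is correct and belongs in the wording of the fix.

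**Conclusion.** The point holds in a limited form. As written, the exploratory models do not distinguish a change in a participant's own employment from stable differences between participants, so the employment coefficient should not be read as employment explaining adherence or relapse.

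Under an assumed trait correlation of 0.3 to 0.5, false rejection is about 4–16% with weekly records and an ICC of 0.2 or more, near nominal for weekly adherence in about 47 MOUD users, and about 12–31% for relapse at nine visits in a logistic model. The ICC, trait correlation and autocorrelation are all assumptions, so no single rate can be asserted.

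A reader might also infer that the adherence and relapse hypotheses are compromised. They are not: those compare the randomized arms and do not rest on this coefficient. Severity is low.

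**What to change.** In the exploratory models, add each participant's mean employment over follow-up beside current and lagged status, or replace those terms by deviations from that mean. Keep study arm in the model. Read the within-person term as the evidence on the role of employment, and report the person-mean term as a descriptive difference between people.

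Add a sentence saying that the within-person term is less precise, because participants whose employment never changes do not inform it. The same sentence should say that it remains open to reverse causation (relapse causing job loss), time-varying confounding and unmodeled serial correlation, so it is not proof of mechanism.

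The cost is one derived variable and a short addition to the analysis text. No new data are needed.

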## Results

Since January 2023, 41 participants have been enrolled and randomized with 25 participants randomized to IPS (10 to site one, 15 to site two) and 16 to non-IPS-VR (3 to site one, 13 to site two). Enrollment will remain open until we achieve our enrollment threshold, no later than August 2025. Tables 1, 2 and 3 describe the baseline and clinical characteristics of the sample to date. To provide a contextual understanding of the study sample, we provide two study vignettes describing two cases, one from each study arm, as shown in Vignettes #1 and #2. Since enrollment and follow-up are still ongoing, no outcomes are presented in this report.

**Table 1 Tab1:** Baseline Demographics and Military History

Variable	IPS (*N* = 25)		Non-IPS-VR (*N* = 16)		Total (*N* = 41)	
	*M*	*SD*	*M*	*SD*	*M*	*SD*
Age (years)	44.4	10	54	11.26	48.2	11.4
Prior-Year Annual Income ($US)	$34,480	$25,587	$16,383	$14,990	$16,383	$14,990
	Frequency	Percent	Frequency	Percent	Frequency	Percent
Sex						
Male	21	84.0	14	87.5	35	85.4
Female	4	16.0	2	12.5	6	14.6
Race						
White	14	56.0	6	37.5	20	48.8
Black or African American	8	32.0	9	56.3	17	41.5
Asian, Mixed, or Other	3	12.0	1	6.3	4	9.8
Ethnicity						
Not Hispanic or Latino	25	100	16	100	41	100
Marital Status						
Single	7	28.0	4	25.0	11	26.8
Married	3	12.0	2	12.5	5	12.2
Divorced	13	52.0	7	43.8	20	48.8
Other	2	8.0	3	18.8	5	12.2
Education						
Less than High School Diploma	1	4.0	–	–	1	2.4
High School Diploma/GED	8	32.0	3	18.8	11	26.8
Vocational Training	11	44.0	11	68.8	22	53.7
Associate or Bachelor’s Degree	5	20.0	2	12.5	7	17.1
Branch of Service						
Army	11	44.0	10	62.5	21	51.2
Navy	9	36.0	2	12.5	11	26.8
Air Force	3	12.0	3	18.8	6	14.6
Other	2	8.0	1	6.3	3	7.3
Period of Service						
Vietnam Conflict	–	–	1	6.3	1	2.4
MAY-1975 to JUL-1990	5	20.0	8	50	13	31.7
Aug-1990 to APR-1991 Gulf War	2	8.0	3	18.8	5	12.2
MAR-1991 to AUG-2001	6	24.0	2	12.5	8	19.5
SEP-2001 to DEC-2010 OIF/OIF	12	48.0	6	37.5	18	43.9
2011 to present	7	28.0	–	–	7	17.1
Combat Exposure						
Served in Combat Zone	14	56.0	7	43.8	21	51.2

*M* Mean, *SD* Standard Deviation, *OIF* Operation Iraqi Freedom, *OEF* Operation Enduring Freedom

**Table 2 Tab2:** Baseline Disability Status, Work History, Number of Dependents, and Housing

Variable	IPS (*N* = 25)		Non-IPS-VR (*N* = 16)		Total (*N* = 41)	
	Frequency	Percent	Frequency	Percent	Frequency	Percent
SSI/SSDI						
Yes	5	20.0	8	50.0	13	31.7
No	20	80.0	8	50.0	28	68.3
Filing for SSI/SSDI	3	12.0	1	6.3	4	9.8
VA Service-Connected Disability Status						
None	10	40.0	6	37.5	16	39.0
Filing for the first time	2	8.0	1	6.3	3	7.3
Filing for appeal	–	–	1	6.3	1	2.4
Receiving any SC disability	10	40.0	8	50.0	18	43.9
Filing for increase	3	12.0	–	–	3	7.3
Receiving 100% SC	6	24.0	3	18.8	9	22.0
Employment Status						
Unemployed	21	84.0	14	87.5	35	85.4
Underemployed	4	16.0	2	12.5	6	14.6
Number of Competitive Jobs Held in the Last 3 Years						
Zero	12	48.0	8	50.0	20	48.8
One	4	16.0	5	31.3	9	22.0
Two	6	24.0	–	–	6	14.6
Three or more	3	12.0	3	18.8	6	14.6
Financial Dependents						
Zero	3	12.0	1	6.3	4	9.8
One	10	40.0	9	56.3	19	46.3
Two	5	20.0	5	31.3	10	24.4
Housing						
Single-family Home	6	24.0	4	25.0	10	24.4
Mobile Home	1	4.0	1	6.3	2	4.9
Apartment or Condominium	5	20.0	2	12.5	7	17.1
Renting Room	3	12.0	1	6.2	4	9.8
Transitional housing	3	12.0	3	18.7	6	14.6
Homeless shelter	3	12.0	4	25.0	7	17.1
Motel	1	4.0	–	–	1	2.4
Residential Treatment	3	12.0	1	6.3	4	9.8
Locality						
Urban	19	76.0	13	81.3	32	78.0
Rural	4	16.0	3	18.8	7	17.1
No response	2	8.0	–	–	2	4.9

*SSI* Social Security Income, *SSDI* Social Security Disability Income, *SC* Service-Connected

**Table 3 Tab3:** Baseline Opioid Use and Treatment History

Variable	IPS (*N* = 25)		Non-IPS-VR (*N* = 16)		Total (*N* = 41)	
	*M*	*SD*	*M*	*SD*	*M*	*SD*
Duration of OUD (years)	10.2	7.9	10.4	12.7	10.3	9.8
	Frequency	Percent	Frequency	Percent	Frequency	Percent
Types of Opioids Used						
Prescription pain pills	19	76.0	11	68.8	30	73.2
Street-derived pills	10	40.0	8	50.0	18	43.9
Street-derived IV, not heroin	2	8.0	1	6.3	3	7.3
Heroin	8	32.0	5	31.3	13	31.7
Current OUD Treatment (past 12 months)						
Any Treatment	21	84.0	10	62.5	31	75.6
Medications for OUD	12	48.0	4	25	16	39.0
Other psychotropic medication	3	12.0	1	6.3	4	9.8
Supportive group therapy	9	36.0	3	18.8	12	29.3
Supportive individual therapy	8	32.0	7	43.8	15	36.6
Complimentary	3	12.0	1	6.3	4	9.8
Inpatient	1	4.0	2	12.5	3	7.3
Residential	5	20.0	5	31.3	10	24.3
Outpatient	2	8.0	2	12.5	4	9.8
OUD Treatment prior to 12 months						
Any Treatment	18	72.0	9	56.3	27	65.8
Medications for OUD	9	36.0	6	37.5	15	36.6
Other psychotropic medication	2	8.0	1	6.3	3	7.3
Supportive group therapy	8	32.0	6	37.5	14	34.1
Supportive individual therapy	8	32.0	8	50.0	16	39.0
Complimentary	1	4.0	3	18.8	4	9.8
Inpatient	6	24.0	4	25.0	10	24.4
Residential	5	20.0	4	25.0	9	22.0
Outpatient	2	8.0	–	–	2	4.8
MINI International Neuropsychiatric Interview						
Major Depressive (current)	3	12.0	1	6.3	4	9.8
Major Depressive (past)	18	72.0	12	75.0	30	73.2
Major Depressive (recurrent)	10	40.0	4	25.0	14	34.1
Agoraphobia (current)	4	16.0	4	25.0	8	19.5
Panic disorder (current)	3	12.0	2	12.5	5	12.2
Panic disorder (lifetime)	8	32.0	5	31.3	13	31.7
Social Anxiety (current)	2	8.0	1	6.3	3	7.3
Obsessive Compulsive (current)	–	–	1	6.3	1	2.4
Posttraumatic Stress (current)	12	48.0	6	37.5	18	43.9
Alcohol use disorder (lifetime)	2	8.0	4	25.0	6	14.6
Alcohol use disorder (past yr)	7	28.0	6	37.5	13	31.7
Substance use disorder (past yr)	17	68.0	10	62.5	27	65.9
Bipolar I (current)	1	4.0	–	–	1	2.4
Bipolar I (past)	–	–	1	6.3	1	2.4
Bipolar II (past)	1	4.0	–	–	1	2.4

*M* Mean, *SD* Standard Deviation, *IPS* Individual Placement and Support, *VR* vocational rehabilitation

## Discussion

The study protocol outlines a rigorous and comprehensive plan for conducting a two-arm, multi-site RCT to evaluate the efficacy of IPS against a credible active control in a large sample of veterans with history of current or lifetime OUD. The growing prevalence of OUD among military veterans is a critical public health concern, with significant consequences for individuals, their families, and society as a whole. A substantial proportion of veterans with OUD face challenges in achieving stable employment and integrating into community settings. Existing evidence supports the efficacy of IPS in improving employment outcomes for individuals with severe mental illness, PTSD, SUD and veterans in a primary care clinic [8, 9, 12–14]. However, its efficacy among veterans with OUD remains relatively underexplored.

The study's rationale is grounded in the need to address this critical gap in the literature. The potential for IPS to facilitate recovery and reintegration into the workforce among veterans with OUD holds immense significance, not only for the affected individuals but also for the healthcare system and society. A successful IPS program could reduce healthcare costs, enhance overall well-being, and strengthen the economic productivity of veterans [41, 42].

This study is innovative in many ways. First, the use of a mixed-method approach allows the investigators to triangulate results and understand the contextual barriers and facilitators of implementing IPS for veterans with OUD. As mentioned earlier, this study is one of the first to examine the efficacy of IPS in this subpopulation of veterans with OUD. Therefore, understanding these barriers and facilitators of implementation may lead to improved implementation of IPS for other SUDs across the VHA. This promises to close the research-translation gaps that often lead to lags in uptake of effective evidence-based interventions for SUD. Secondly, the use of a CBPR approach allows the integration of multiple stakeholders and partners in informing implementation strategies, thereby leading to greater buy-in. The veteran’s feedback is intentionally and systematically incorporated to ensure a whole health approach to the implementation of IPS among veterans with OUD. Moreover, the goal to examine how employment outcomes inform other psychosocial outcomes is important in our understanding of the mechanisms through which IPS improves community integration. Lastly, to our knowledge and from an extensive review of the literature, our study would be the first to explore the relationship between vocational rehabilitation services, employment and MOUD adherence. This is very important as we know that MOUD adherence is a predictor of positive treatment outcomes among people with OUD [43, 44].

### Implications for practice

The results of this study, if positive, will have far-reaching implications for clinical practice and service delivery in veteran healthcare, and will hopefully lead to better VR services in community-based settings and the general population. A successful IPS intervention would offer a promising and evidence-based approach to improving the vocational outcomes of veterans with OUD. Mental health and addiction treatment providers, as well as VA service organizations, would benefit from guidance on the integration of IPS programs into existing care pathways. It may also foster interagency collaborations to address the complex needs of this population. Incorporating IPS into the continuum of care could empower veterans to achieve stability in their employment, which, in turn, is expected to have a positive impact on other domains of their lives, such as housing stability and overall quality of life [20, 45]. This, in turn, has the potential to reduce the burden on mental health and addiction treatment services, as well as decrease the rates of relapse among veterans [46, 47].

A positive outcome in this study may not only transform the way care is delivered to veterans with OUD but also inform strategies for addressing employment challenges in other populations with SUDs. Furthermore, it underscores the importance of integrated and patient-centered care approaches that consider not only the medical aspects of OUD but also the social determinants that significantly influence an individual's recovery, specifically employment.

This multi-site RCT represents a significant step toward enhancing the evidence base for interventions that can improve the vocational outcomes of veterans with OUD. By addressing these challenges, our research seeks to contribute to the betterment of the lives of those who have served their country and to inform the development of more comprehensive and effective interventions in the field of addiction treatment and vocational rehabilitation.

### Study limitations

The study protocol acknowledges several methodological challenges. Randomized controlled trials offer a robust design for evaluating intervention efficacy, but this approach is not without its limitations. Blinding among participants and study staff is not possible, given the nature of the IPS intervention. However, both IPS and non-IPS VR interventionists have received extensive training to ensure fidelity to intervention arms.

The study also faces potential limitations in terms retention of participants and generalizability. Veterans with OUD are a diverse group, and the study population may not fully represent the entire spectrum of this population. Data collection across multiple sites may introduce variability in intervention fidelity and outcome measurement, which could impact the overall findings.

Over the course of a multi-site trial, it can be challenging to maintain consistent follow-up because of attrition that may lead to missing data, potentially biasing the results. We minimize these potential limitations by keeping assessments to a minimum to reduce the burden on the participant. Finally, the study may be limited by resource constraints, including time and turn-over in personnel which could affect implementation of the intervention and data collection. Given that the sites are within 60 miles of each other and use shared technology, providing temporary coverage for study personnel turnover mitigates these vulnerabilities.

